### Participant timeline {13}

After randomization, patients will receive the allocated interventions for 7 continuous days and be followed up for 6 months. The study schedule includes a screening visit; four treatment visits on day 1, 3, 7, and 14; and three follow-up visits on day 28, 3, months and 6 months. We will collect the patients’ survival status at follow-up visits. The participant timeline is shown in Table 3.

**Table 3 Tab3:** Schedule of screening, intervention and follow-up of the trial

Study periods	Screening	Treatment periods						Follow-up periods		
Time line		d1	d3 + / − 1	d4 to d6^a^	d7 + / − 1	d8 to d13^a^	d14 + / − 2	D28^a^ + / − 3	3 M^a^ + / − 7	6 M^a^ + / − 7
Consent form	X									
Check with inclusion and exclusion criteria	X									
Demographic characteristics	X									
Symptoms	X	X	X	X	X	X	X	X	X	X
Vital sign	X	X	X		X		X			
Adverse event		X	X	X	X	X	X			
Viral load		X	X		X		X			
Chest image (DXR or CT)		X			X		X	X		
Pregnancy test	X						X			
Blood routine	X	X	X		X		X			
Ferritin		X								
Interleukin-6		X								
Hypersensitive C-reactive protein		X	X		X		X			
Blood biochemical test	X	X	X		X		X			
Coagulation		X			X					
Oxygen level	X									
Cardiac troponin and N-terminal pro-brain natriuretic peptide		X			X					
Concomitant medication		X								

^a^Visits by phone calls

### Sample size {14}

This study aims to determine the efficacy of a new antiviral compared to placebo in reducing critical illness or all-cause mortality on day 28 in COVID-19 patients.

The sample size was calculated based on the superiority test. The primary endpoints are the disease critical rate and mortality rate. Based on the data reported in Hong Kong for patients with COVID-19 from the end of 2020 to March 2022, the number of deaths and serious illnesses was 6866 and 8875, respectively [21]. Previous data on another antiviral drug, Paxlovid, showed that the placebo group had 65 hospitalizations and 12 deaths, while the Paxlovid group had no deaths and 8 hospitalizations [5]. Combined with data from Hong Kong, it was speculated that there may be 15–16 severe patients in the placebo group and 2 severe patients in the Paxlovid group. Therefore, the disease critical rate and mortality rate in other countries and China are assumed to be 2.6% in the standard treatment group and can be reduced to 0.19% with effective treatment. With a power of 90% (1 sided *α* = 0.025 and *β* = 0.10), a sample size of 986 patients in each group is needed. The sample size calculations were performed using SAS software, version 9.4 (SAS Institute Inc., USA).

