### Outcomes {12}

The primary outcome of this trial is the ratio of COVID-19-related critical illness and all-cause mortality among the two groups within 28 days. COVID-19-related critical illness is defined as a patient who requires mechanical ventilation or extracorporeal membrane oxygenation or a patient maintaining oxygen saturation (SpO_2_) above 90% who requires high-flow oxygen inhalation with a fraction of inspired oxygen (FiO_2_) not less than 60% or requires noninvasive ventilation with a FiO_2_ not less than 60%.

The secondary outcomes are as follows: (1) COVID-19 viral load measured from pharyngeal swabs at the D1, D3, D7, and D14 timepoints, (2) incidence of azvudine-related adverse events (AEs) and serious adverse events, (3) duration of COVID-19-related symptoms, (4) all-cause mortality within 6 months, (5) days of hospitalization and intensive care unit stay, and (6) the ratio of COVID-19-related severe illness defined on the China Formula of Diagnosis and Treatment for COVID-19 (trial version 10). In detail are as follows: (1) shortness of breath with respiratory rate ≥ 30 breaths/min, (2) SpO_2_ ≤ 93% when inhaling air at rest, (3) partial pressure of arterial oxygen/FiO_2_ ≤ 300 mmHg, and (4) progressive worsening of clinical symptoms and obvious lesion progression > 50% on chest imaging within 24 to 48 h.

The safety endpoints consist of adverse events that emerge during or after the treatment period and subsequent observation period until 28 days. SAEs and AEs leading to discontinuation of the trial drug or placebo will be coded according to the definition of severe adverse events published by the FDA (https://www.fda.gov/safety/reporting-serious-problems-fda/what-serious-adverse-event).

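### The planned rates of 2.6% and 0.19% add deaths to severe cases and are relabelled as critical illness and mortality, so the single 90% power is not shown to apply to the primary endpoint

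*Protocol article*

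**What the plan says.** Sample size {14} names its target: "The primary endpoints are the disease critical rate and mortality rate". Its inputs are of another kind. For Hong Kong, "the number of deaths and serious illnesses was 6866 and 8875, respectively". For an earlier antiviral trial it gives 65 hospitalizations and 12 deaths on placebo, against 8 and none on active treatment. Combining the two sources, "it was speculated that there may be 15–16 severe patients in the placebo group and 2 severe patients in the Paxlovid group". The next sentence opens with a therefore and concludes that "the disease critical rate and mortality rate in other countries and China are assumed to be 2.6% in the standard treatment group", falling to 0.19% with effective treatment.

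Outcomes {12} separates the grades. For the primary endpoint, "COVID-19-related critical illness is defined as a patient who requires mechanical ventilation or extracorporeal membrane oxygenation", or who, to hold oxygen saturation above 90%, "requires high-flow oxygen inhalation with a fraction of inspired oxygen (FiO_2_) not less than 60" per cent, or noninvasive ventilation at that same level. All-cause death within 28 days completes the composite. Secondary outcome (6) is "the ratio of COVID-19-related severe illness defined on the China Formula of Diagnosis and Treatment for COVID-19 (trial version 10"). Its criteria are a respiratory rate of at least 30, saturation of 93% or less on room air, PaO2/FiO2 of 300 mmHg or less, or clinical worsening with imaging progression.

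**The concern.** The grade of illness changes between the inputs and the conclusion. The paragraph begins with serious illnesses, passes through severe patients and ends with a critical rate, and nothing is said about how many of the first two would count as the third. None of the criteria for secondary outcome (6) requires respiratory support, whereas every route to critical illness does. It is a fair inference, though the protocol does not state it, that critical illness is the narrower category.

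The trial expects few primary events: 2.6% of 493 is about 13 in the control arm. If some of the cases behind the 2.6% would not meet the primary definition, the planned control rate is too high and the power is lower than planned. A null result would then be read against a 90% figure that the document does not support for this endpoint.

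**Working it through.** **Reproducing the plan's sample size.** Inputs from Sample size {14}: p1 = 0.026, p2 = 0.0019, one-sided alpha 0.025, power 90%. With the unpooled two-proportion formula,

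n = (1.960 + 1.282)² × [p1(1−p1) + p2(1−p2)] / (p1−p2)² = 10.507 × 0.02722 / 0.0241² = 492.4,

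which rounds up to 493 per arm and 986 in total. Then 986/0.9 = 1,096, the figure in Recruitment {15}. The 986 is worded as a per-group number but fits only as the total; that is a separate matter, and 493 per arm is used below.

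**Rebuilding the rates.**
- Severe cases on placebo: 12 × 8875/6866 = 15.5, the plan's 15–16.
- Severe cases on active treatment: 15.5 × 8/65 = 1.9, the plan's 2.
- Arm size implied by the active rate: 2/0.0019 = 1,053 (inferred; the protocol gives no denominator).
- Control rate: (12 + 15.5)/1,053 = 2.61%, matching 2.6%. Severe cases alone would give 15.5/1,053 = 1.47%, which does not match.
- Active rate: (0 + 2)/1,053 = 0.19%.

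So the planned rates are deaths plus severe cases. Deaths make up 12/27.5 = 44% of the control events, and the other 56% carry the question of grade.

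**Effect on power.** Let f be the share of the severe cases that meet the critical definition in Outcomes {12}. This is an assumption, because the documents give no value. Keep all deaths, so p1 = (12 + 15.5f)/1,053. The treated rate can be scaled in two ways: (a) from the plan's counts, p2 = 2f/1,053; (b) at the plan's relative risk, p2 = p1 × 0.19/2.6 = 0.073 × p1.

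Unpooled formula: power = Φ(√{493 (p1−p2)² / [p1(1−p1) + p2(1−p2)]} − 1.96). At f = 0.5 under (a), p1 = 19.75/1,053 = 1.88% and p2 = 1/1,053 = 0.09%, so power = Φ(2.84 − 1.96) = 81%. The chi-square column is exact binomial enumeration of the uncorrected test at one-sided 0.025.

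| f | p1 | p2 (a) | Unpooled (a) | Chi-square (a) | Unpooled (b) | Chi-square (b) |
|---|---|---|---|---|---|---|
| 1 | 2.61% | 0.19% | 90% | 95% | 90% | 95% |
| 0.5 | 1.88% | 0.09% | 81% | 90% | 78% | 86% |
| 0.25 | 1.51% | 0.05% | 75% | 86% | 69% | 77% |
| 0 | 1.14% | 0 | 66% | 81% | 57% | 64% |

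The 86% at f = 0.25 under (a) becomes 87% if the unrounded 1.9 treated cases replace 2. Fisher's exact test is more conservative: 80%, 69% and 49% under (a) at f = 0.5, 0.25 and 0. None of these figures allows for the planned interim analysis.

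**The case against.** A reader might infer that the 90% really belongs to a different endpoint, severe illness or death, and that the trial is therefore underpowered. The documents do not support that. Sample size {14} explicitly assigns its rates to critical illness and mortality, so the power is nominally for the primary endpoint. What is missing is the support for that assignment. The paragraph does not cite the criteria of secondary outcome (6), and the article uses severity terms loosely: the Discussion describes the evidence gap first as severe illness and death and, in the next sentence, as critical disease and mortality. The Hong Kong category is not defined. Its ratio of deaths to serious illnesses, 6866/8875 = 0.77, is compatible with a category close to critical illness, in which case f is near 1 and little is lost. All of this stands.

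Nor is the rate made of severe illness alone, since the deaths in it are proper primary events.

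The size of any loss also depends on the test. The protocol plans a log-rank comparison, which with follow-up to day 28 behaves much like the uncorrected chi-square. On that test, power stays near 90% at f = 0.5 under scaling (a). The lower figures come from a normal approximation at small event counts, or from Fisher's test. That stands too, although at a constant relative risk the chi-square figure falls to 86% at f = 0.5 and 77% at f = 0.25.

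Finally, the interim sample size re-estimation softens the consequence of an uncertain planning rate. It does not make the stated 90% correct. It also needs no correction on this account, because Interim analyses {21b} never proposes to use severe illness.

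**Conclusion.** The point holds in a limited form. The plan sums deaths and severe cases, calls the sum a critical-illness-and-mortality rate, and gives no conversion, although its own outcomes section keeps the grades apart. The 2.6% and 0.19%, and with them the single 90%, are unsupported for the primary endpoint; they are not shown to be wrong. There is no shortfall at f = 1. Across f from 1 to 0 the power runs from 90% down to 66% or 57% by the plan's own formula, and from 95% down to 81% or 64% by the test nearest the planned one; the lower figure in each pair assumes a constant relative risk. These ranges rest on an inferred arm size of about 1,053, on the plan's adding of deaths and severe cases without overlap, and on an f that the documents do not give. The sample size arithmetic itself is sound once 986 is read as the total; the weakness lies in a planning assumption.

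**What to change.** In Sample size {14}:
- State that 2.6% and 0.19% are deaths plus severe or serious cases as the sources define them, and say what those definitions are.
- State the assumed share f of those cases that would meet the critical-illness definition in Outcomes {12}, with the reason for it.
- Replace the single 90% with the power of the existing size (493 evaluable per arm) as a function of f, calculated for the planned type of test, and say how the treated rate is assumed to scale.

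If the source category turns out to match the critical definition, one sentence saying so settles the matter. The change is a rewording of one paragraph. It adds no patients and leaves the endpoint, the analysis and the interim plan as they are. The price is a conditional and, unless f is close to 1, less favourable power statement.

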## Statistical methods

### Statistical methods for primary and secondary outcomes {20a}

All data will be analysed using SAS software, version 9.4 (SAS Institute Inc., USA). A two-tailed *p* < 0.05 will be considered statistically significant in all statistical tests (except for the main efficacy indicators and other specified instructions).

The full analysis set (FAS), modified intention-to-treat set (mITT), per-protocol set (PPS), and safety set (SS) will be divided for analysis. FAS includes all eligible and randomized patients. PPS includes eligible patients with better compliance (80–120%), and completing necessary items of CRF.SS includes all patients enrolled in the study who have received at least one dose of medication and have at least one safety evaluation. Baseline characteristics analysis will be based on FAS, efficacy analysis will be based on FAS and PPS, and safety analysis will be based on SS. Unblinded patients will be excluded from PPS.

Continuous data will be summarized as the mean ± standard deviation, median, minimum, maximum, lower quartile, and upper quartile. Categorical data will be presented and summarized as frequencies and percentages in each category.

Between-group comparisons will be conducted by using paired *t*-tests or Wilcoxon rank tests for continuous data, chi-square tests or Fisher exact tests for categorical data, Wilcoxon rank tests or CMH tests for ranked data, and Kaplan‒Meier estimates for time-to-event data. The principles of intention-to-treat analysis will be used.

Efficacy analysis will be based on FAS and PPS. The primary efficacy endpoints are COVID-19-related critical illness and all-cause mortality within 28 days (whichever happens first), which will be analysed based on a time-to-event manner. Kaplan‒Meier method will be used to describe the incidence rates of the primary endpoint in each group separately at 28 days. Between-group comparisons will be performed by the log rank test. A Cox regression model will be used to estimate the hazard ratio and corresponding 95% confidence interval and adjust for potential covariates such as centres. Secondary efficacy endpoint analysis will be performed according to general statistical considerations. The specifics of these methods will be thoroughly outlined in the statistical analysis plan.

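### The 2.6% placebo rate is reached only by adding 12 deaths to 15–16 severe cases, so the stated 90% power holds only if no patient is in both counts (about 60% if all the deaths overlap)

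*Protocol article*

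**What the plan says.** Sample size {14} builds its planning rates from two sources. For Hong Kong, "the number of deaths and serious illnesses was 6866 and 8875, respectively". For the earlier nirmatrelvir-ritonavir trial, "the placebo group had 65 hospitalizations and 12 deaths", against 8 hospitalizations and no deaths on active drug. The section combines these into a guess of 15–16 "severe patients in the placebo group and 2 severe patients in the Paxlovid group". It then concludes that "the disease critical rate and mortality rate in other countries and China are assumed to be 2.6% in the standard treatment group". For the treated group it puts the rate at 0.19%.

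The error rates are "1 sided *α* = 0.025 and *β* = 0.10", that is, 90% power. The resulting 986 is printed as a per-group figure. Recruitment {15} inflates it for 10% dropout to 1,096 in total, 548 per arm.

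Statistical methods {20a} defines the primary endpoint as "COVID-19-related critical illness and all-cause mortality within 28 days (whichever happens first"), so a patient who becomes critically ill and later dies contributes one event.

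**The concern.** The step from counts to percentages is not shown. No arm size is printed, and the section does not say whether the serious illnesses include patients who later died. The severe counts alone do not give 2.6% on the base that 0.19% implies. If deaths were added to severe cases and some patients are in both groups, those patients are counted twice in the planning rate but would be counted once in the trial.

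The placebo rate drives the power claim. If it is too high, the trial is weaker than its stated 90%, and a null result would be read with more confidence than it deserves. Interim analyses {21b} also plans futility and sample size re-estimation, for which the planning rate is the natural point of comparison.

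**Working it through.** **Inputs.** All are from Sample size {14} and Recruitment {15}: 6,866 deaths and 8,875 serious illnesses (Hong Kong); 65 hospitalizations and 12 deaths (placebo), 8 and 0 (active); 15–16 and 2 severe cases; rates 2.6% and 0.19%; one-sided α 0.025; power 90%; 986 before and 1,096 after 10% dropout; 548 per arm.

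**1. Reproduce the sample size.** Two proportions, unpooled variance:
- n = (1.960 + 1.282)² × [0.026 × 0.974 + 0.0019 × 0.9981] / (0.026 − 0.0019)² = 10.507 × 0.02722 / 0.0241² = 492.4, so 493 per arm and 986 in total.
- 986 / 0.90 = 1,096, which is 548 per arm.

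So 986 works as the total, and 493 evaluable per arm is used below.

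**2. Reproduce the severe counts.**
- Placebo: 12 × 8,875 / 6,866 = 15.5, which matches 15–16. The severe cases are the 12 deaths scaled by the Hong Kong ratio.
- Active: 8 × 15.5 / 65 = 1.9, which matches 2.

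**3. Infer the denominator.** 2 / 0.0019 = 1,053 (1,026 to 1,081 allowing for rounding of 0.19%). This is an inference; the protocol prints no arm size.

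**4. Candidate rates on 1,053.**

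| Count | Rate |
|---|---|
| Active: 2 severe + 0 deaths | 0.19% |
| Placebo: 12 deaths only | 1.14% |
| Placebo: 15–16 severe only | 1.42–1.52% |
| Placebo: 15.5 severe + 12 deaths = 27.5 | 2.61% |
| Placebo: 65 hospitalizations | 6.2% |

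Only the sum gives 2.6%.

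**5. Effect of overlap.** Patients with at least one event = 15.5 + 12 − (deaths already among the severe). Power uses the pooled two-proportion formula: Φ{[(p₁ − p₂)√n − 1.960·√(2p̄(1 − p̄))] / √[p₁(1 − p₁) + p₂(1 − p₂)]}, with n = 493, p₂ = 0.0019 and p̄ the mean of p₁ and p₂.

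| Deaths among the severe | Patients | p₁ | Power |
|---|---|---|---|
| 0 | 27.5 | 2.61% | Φ(1.28) = 90% |
| 6 | 21.5 | 2.04% | Φ(0.81) = 79% |
| 12 | 15.5 | 1.47% | Φ(0.26) = 60% |

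For the whole 15–16 range at full overlap, power is 58–62%. With all 548 per arm evaluable, power at 1.47% is 65%. Reaching 90% there would take about 1,052 per arm, which shows how sensitive the design is and is not a request.

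**6. Check by exact enumeration.** At 493 per arm the z test has 95% power at 2.6% and 64% at 1.47%; Fisher's test has 92% and 49%. The levels shift with the method, but the size of the drop does not depend on the normal approximation. The Schoenfeld formula gives higher values (81–86% at 1.42–1.52%), but with about 493 × (0.0147 + 0.0019) = 8 expected events it is not reliable.

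**The case against.** The strongest reply is that one denominator and one rule (severe plus deaths) reproduce both rates: 27.5/1,053 = 2.61% and 2/1,053 = 0.19%. This stands. A reader might infer that neither rate follows from the counts, because 15–16 against 2 is a 7.5- to 8-fold difference while 2.6% against 0.19% is 13.7-fold. Adding the deaths explains the gap (27.5/2 = 13.75), and deaths belong in the composite. The doubt concerns 2.6% only.

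A reader might also infer that double counting has occurred. The protocol does not establish that. It lists deaths and serious illnesses as two numbers and does not say whether they share patients. If they are separate, 2.6% is a correct composite rate and power stays at 90%. Scaling the severe cases from the deaths makes overlap plausible but does not prove it.

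The denominator is inferred. If 15.5 cases were themselves 2.6%, the placebo arm would be about 15.5/0.026 = 596. With arms of similar size, 2 treated cases would then be 0.34%, not 0.19%, and power would be 84%. That reading avoids adding deaths but contradicts the printed treated rate.

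Read literally as per group, 986 would give 88% power at 1.47%. Recruitment {15}, with 548 per arm, rules that reading out for the trial as planned.

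Finally, the planned re-estimation might respond to a low event rate. Its rule is not shown, so it can be taken neither as a remedy nor as already compromised.

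**Conclusion.** The point holds in conditional form. On the denominator implied by 0.19%, the 2.6% placebo rate comes from adding 12 deaths to 15–16 severe cases. This suits a first-event composite only if the two groups share no patient, a condition that the protocol neither states nor supports. Power is 90% under zero overlap, about 79% if half the deaths overlap and about 60% under full overlap. The last figure is the worst case, not a central estimate.

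This rests on three assumptions: an arm size of about 1,053, the treated rate held at 0.19%, and 493 evaluable patients per arm. The document does not allow a choice within the 60–90% range. It would be wrong to conclude that true power is 60% or that an error in 2.6% has been demonstrated. What is shown is that the 90% claim depends on an unstated condition with a large effect.

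**What to change.** In Sample size {14}:
- Rederive the placebo rate with each patient counted once. Print the denominator and say whether the severe cases include patients who died.
- Restate the 90% power as conditional on zero overlap, and give the power of the 1,096-patient design at the rederived rate. Until the overlap is known, the supportable range is about 60–90% over placebo rates of 1.5–2.6%, labelled as resting on an inferred arm size.
- Print 986 as the total, in line with 548 per arm in Recruitment {15}.

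Use the rederived rate as the planning reference for the re-estimation in Interim analyses {21b}.

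The cost is rewording and a look back at the source counts. The stated power may become less favourable. No extra patients are requested.

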### Trial design {8}

This is a prospective multicentre, placebo-controlled, randomized, double-blind phase III trial, with a superiority design. A total of 1096 symptomatic adult patients with COVID-19 infection who are at increased risk of progressing to critical illness, based on their demographics and comorbidities, will be recruited from January 2023 through January 2024 [5]. The patients will be randomized at a 1:1 ratio to the treatment group and placebo group and treated with azvudine and placebo, respectively (Additional file 1). The investigator will observe and record subjects’ disease progression or remission and adverse drug reactions and analyse the data. Double blinding will be used in the trial.

This protocol was designed according to the Standard Protocol Items: Recommendations for Interventional Trials (SPIRIT) 2013 Statement (Additional file 2) [18] and registered at ClinicalTrials.gov (ID: NCT05689034).

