### Recruitment {15}

To account for a 10% dropout rate, the sample size increased to 1096 participants (548 in the azvudine group and 548 in the control group). To enrol enough participants, we set up special screening staffs in the fever clinic and emergency department where COVID-19 patients often visit, and screening staffs distribute COVID-19 antigen to suspected fever patients to identify candidates. In order to complete such large amount patients’ selection as soon as possible, we selected 46 study sites localized in 17 different provinces in China Mainland; thus, we will obtain timely enrolment to the greatest extent possible.

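### The 986 patients stated as needed in each group are the total for both groups (493 per group); read literally, the protocol plans half the size it says 90% power requires

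*Protocol article*

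**What the plan says.** The Sample size section ({14}) takes the 28-day rate of critical illness or death under standard treatment from external data. The rates "are assumed to be 2.6% in the standard treatment group" and "can be reduced to 0.19% with effective treatment". The error rates are "1 sided *α* = 0.025 and *β* = 0.10". From these it concludes that "a sample size of 986 patients in each group is needed". No formula is named beyond the statement that "The sample size was calculated based on the superiority test".

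The next section, Recruitment ({15}), allows for 10% dropout and reports that "the sample size increased to 1096 participants (548 in the azvudine group and 548 in the control group"). Trial design ({8}) agrees: "A total of 1096 symptomatic adult patients with COVID-19 infection", randomised 1:1. The Abstract gives the same total, and Table 2 lists 548 participants in each arm.

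**The concern.** A requirement of 986 evaluable patients per group cannot grow, after an allowance for dropout, into 548 randomised per group. One of the two adjacent sections must be wrong.

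If the Sample size section were right, the trial would be randomising far too few patients for its stated power. If the Recruitment section is right, the Sample size section misstates its own result by a factor of two. The reader needs to know which, because this sentence is the protocol's only statement of the size needed for 90% power. An ethics committee or data monitoring committee that took it at face value would conclude that the trial is badly undersized.

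**Working it through.** **Inputs, all from Sample size {14} unless noted**

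- Control rate p1 = 0.026; treatment rate p2 = 0.0019; difference 0.0241.
- One-sided α = 0.025, so z = 1.960; power 90%, so z = 1.2816.
- Allocation 1:1 (Trial design {8}).
- Dropout 10% (Recruitment {15}).

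**Step 1: trying to reproduce 986**

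Unpooled two-proportion formula:

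n per group = (z_α + z_β)² × [p1(1 − p1) + p2(1 − p2)] / (p1 − p2)²

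= (1.960 + 1.2816)² × (0.026 × 0.974 + 0.0019 × 0.9981) / 0.0241²

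= 492.4, rounded up to **493 per group, 986 in total**.

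The stated number is matched exactly, but as a total.

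**Step 2: could another method give 986 per group?**

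| Method (one-sided 0.025, 90% power) | n per group |
|---|---|
| Unpooled z-test | 493 |
| Pooled z-test | 496 |
| Pooled, continuity-corrected | 576 |
| Arcsine | 376 |
| Log-rank events, Schoenfeld | about 251 |
| Log-rank events, Freedman | about 538 |

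Other readings of α were also tried. The largest result was 667 per group (two-sided 0.025 with continuity correction). None comes near 986 per group.

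**Step 3: the dropout step**

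- 986 read as the total: 986 / 0.90 = 1,095.6, rounded up to **1,096**. Per group, 493 / 0.90 = 547.8, rounded up to **548**. Both match Recruitment {15}.
- 986 read as per group: 1,972 / 0.90 = 2,191.1, rounded up to **2,192**. This is exactly twice the plan.

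**Step 4: power at each size**

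| Patients per group | Power, pooled z-test |
|---|---|
| 493 | 89.8% |
| 548 | 92.6% |
| 986 | 99.6% |

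At 493 per group the unpooled formula gives 90.0% and Fisher's exact test 91.7%. So 493 is the size that corresponds to the stated 90%, and 986 per group is not.

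**The case against.** The strongest reply is that this is one mislabelled phrase with no operational effect. Every figure that governs conduct agrees: 1,096 in the Abstract and in Trial design, 548 per arm in Table 2 and in Recruitment. The planned size delivers the stated power under the stated rates, and a reader who goes on to the next section can resolve the conflict with one division. All of this is true, and the point should not be read as a finding that the trial is underpowered.

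It could also be argued that the error might mislead the sample-size re-estimation described under Interim analyses ({21b}). The document does not support going that far. The interim is set at 548 participants in the mITT set, which is half of 1,096 and so fits 1,096 as the planned total. Nothing ties the re-estimation to 986 per group, and its method would normally be in the statistical analysis plan, which is not shown.

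Two matters of precision also stand. The planned size is exactly half the literal requirement only after the dropout allowance (1,096 of 2,192); against the evaluable requirement it is 1,096 / 1,972 = 56%. And the match to 986 is exact only for the unpooled formula; the pooled formula gives 992 in total.

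None of this removes the contradiction, and no method tried supports 986 per group.

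**Conclusion.** The concern holds. The Sample size section states a per-group requirement that is twice what its own inputs give and that contradicts the Recruitment section. The dropout arithmetic and the re-derivation independently identify 986 as the total, with 493 per group.

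Read literally, the sentence implies 2,192 randomised patients instead of 1,096, and about 99.6% power instead of 90%. The actual plan of 548 per group, or 493 evaluable after 10% dropout (548 × 0.90 = 493.2), gives about 90% power.

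This rests on the protocol's assumed rates of 2.6% and 0.19%, taken as given, and on comparing two proportions at 28 days. Whether those rates are plausible is a separate question. The remedy is editorial, but the figure is the basis of the trial's stated power and is wrong as written, so it must be corrected.

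**What to change.** In Sample size {14}, restate the requirement as 986 patients in total, 493 in each group. Leave Recruitment {15} unchanged: 1,096 after 10% dropout, 548 per group. Naming the formula in the same sentence would let a reader reproduce the number; the unpooled two-proportion test matches it exactly, but the sponsor should confirm that this is what was used.

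The cost is a one-line correction. Enrolment, allocation and analysis do not change.
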